## Timeframe

The trial is set to start including participants as soon as ethical clearance is obtained (e.g. by October 2017), since the underlying BuDiLoLo study has already started screening subjects. The recruitment phase ends once sufficient participants (n=42) are included for the overall design of the trial. The duration of the recruitment phase thus depends partially on the screening rate in BuDiLoLo, but is anticipated not to exceed ~2 months. Arms 1 and 2 of the trial will commence as soon as recruitment is completed and randomization is performed. Arms 3 and 4 will commence in parallel thereafter. Follow-up in each study arm will last 6 months. Thus the total duration of the trial is anticipated to be ~9-10 months.

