## Study size

This study is a descriptive study and is not powered for statistical testing of a predefined hypothesis. As a proof of principle study, this trial aims to describe the crude effect of respective treatment regimens on the proportion of subjects achieving sustained reduction in peripheral microfilaraemia and on the kinetics of parasitaemia. For this purpose a total of 8 evaluable subjects per treatment arm is required at the end of 6-months’ follow-up. In order to allowing for up to ⅓ (33%) loss to follow-up during this period, 12 patients will be recruited into each treatment group. An additional 6 patients will be recruited for the control group for the description of the natural variability of microfilaraemia. Thus the total study size will be 42 participants: n=6 in study arm 1 and n=12 each in arms 2-4. In case of drop out of more than 33% in any study arm for evaluation of the primary endpoint, further patients will be screened and included in the respective study arm to achieve at least 8 evaluable patients in each treatment group.

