## Inclusion criteria

- Adult, participants of either sex
- *L. loa* microfilaria < 50,000 mf/mL
- Intention to remain residing in study area and comply with study procedures throughout 6 month follow-up period
- Signed written informed consent

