### Randomisation and start of study arms

Once sufficient participants are included for the entire study, participants will be randomized to one of the four study arms. The generation of the randomization sequence will be computer assisted with a block size of 10 with a fixed allocation of 12 patients for each treatment arm and 6 for the control group. The randomisation list will be produced by a team independent of the investigators and will be provided as sealed opaque envelopes to the study team. The investigator may only open the sealed opaque envelope after informed consent has been obtained and the subject is to be allocated to a treatment arm. Treatment allocation will then be revealed to the subject. No change of treatment allocation will be permitted in the course of this trial. If it is in the interest of the patient safety, the patient will be removed from the study and will receive appropriate routine care. In case of requirement of allocation of extra-patients to a study arm due to excessive loss-to-follow-up, patients will be screened and will be allocated to the respective treatment arm without randomization. This fact will be clearly acknowledged in the analysis and presentation of the data.

At the first visit of their study arm (DT0), each participant will again have blood drawn for laboratory safety parameters (haematology and biochemistry) and for quantification of *L. loa* microfilaraemia. In addition, blood may be collected for immunology (baseline). Participants in arms 2, 3 & 4 will receive their first dose of albendazole under supervision.

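### The one-third loss allowance omits the interval between open randomisation and the later start of arms 3 and 4, so those two arms are more exposed to the plan's non-randomised top-up

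*Protocol*

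**What the plan says.** **Size.** Protocol section 5.2 (Study size) states that "a total of 8 evaluable subjects per treatment arm is required at the end of" the 6-month follow-up. Allowing for up to one-third "loss to follow-up during this period, 12 patients will be recruited into each treatment group", it arrives at: "the total study size will be 42 participants: n=6 in study arm 1 and n=12 each in arms 2-4". If an arm loses more than 33% of its people as regards the primary endpoint, the stated remedy is: "further patients will be screened and included in the respective study arm to achieve at least 8 evaluable patients in each treatment group". Section 6.2 (Randomisation and start of study arms) adds that these extra patients enter the arm without randomisation and that the analysis will acknowledge this.

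**Clock.** Follow-up runs for 6 months from each arm's own start (sections 4.1 and 4.4). The 6-month primary endpoint is timed from the start of treatment (section 4.3.1).

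**Order of events.** Everyone is recruited first and then randomised. Arms 1 and 2 begin as soon as that is done. For the others, section 4.4 says: "Arms 3 and 4 will commence in parallel thereafter". No interval is given. On opening the envelope, "Treatment allocation will then be revealed to the subject".

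**Duration.** Recruitment is expected to take no more than about 2 months, and "Thus the total duration of the trial is anticipated to be ~9-10 months" (section 4.4).

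**Residence.** Section 5.3 requires "Intention to remain residing in study area and comply with study procedures throughout 6 month follow-up period".

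**The concern.** The loss allowance and the randomisation start at different times. The allowance starts when an arm starts. The randomised group is fixed earlier, before arms 1 and 2 begin. For arms 1 and 2 the two moments nearly coincide. For arms 3 and 4 there is a gap in which people are already allocated, know their arm and have received no study drug, and section 5.2 makes no provision for losing them.

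Two things are at stake.

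- **Replacement of randomised by non-randomised people.** A person who leaves before the first treatment day (DT0) cannot contribute to the primary endpoint. Each such departure in arm 3 or 4 brings the arm closer to the top-up, which is filled without randomisation.
- **Departure that depends on the arm.** Arms 3 and 4 start in parallel and differ only in the second intervention, so they are the cleanest pair in the trial. During the wait, one group knows it is due a second albendazole course and the other that it is due ivermectin, a drug whose severe reactions at high microfilarial load the protocol describes in section 3.2.2. If the two groups leave for different reasons, their comparability is weakened before any drug is given.

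**Working it through.** **1. The plan's own figure.** Inputs from section 5.2: 8 evaluable, loss of 1/3.

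8 / (1 − 1/3) = 12 per treatment arm, and 6 + 3 × 12 = 42. Both figures reproduce. There is no slack: 12 × 2/3 = 8.0 exactly.

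**2. Length of the wait.** It is not stated. From section 4.4: total of 9 to 10 months, minus 2 for recruitment, minus 6 for follow-up, leaves 1 to 2 months. This is a remainder of approximate figures.

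**3. Without assuming any loss rate for the wait.** Suppose the full one-third is lost after arm start, and k of 12 people leave before it:

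- k = 1: 11 × 2/3 = 7.3 expected evaluable
- k = 2: 10 × 2/3 = 6.7 expected evaluable

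At the planned ceiling, a single departure during the wait takes the expected number below 8.

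**4. With an assumed rate.** Assumption: the monthly loss implied by the 6-month figure d also applies during a wait of w months.

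- Retention: S = (1 − d)^((6 + w)/6)
- Expected evaluable: 12 × S
- Chance of fewer than 8: P(X ≤ 7), with X binomial(12, S)

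For d = 1/3 the monthly loss is 1 − (2/3)^(1/6) = 6.5%. Over a wait of 1 or 2 months that is 6.5% or 12.6%, or 0.8 or 1.5 of 12 people before DT0.

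| 6-month loss d | Wait (months) | S | Expected evaluable of 12 | P(fewer than 8) |
|---|---|---|---|---|
| 1/3 | 0 | 0.667 | 8.0 | 37% |
| 1/3 | 1 | 0.623 | 7.5 | 50% |
| 1/3 | 2 | 0.582 | 7.0 | 61% |
| 25% | 0 | 0.750 | 9.0 | 16% |
| 25% | 1 | 0.715 | 8.6 | 24% |
| 25% | 2 | 0.681 | 8.2 | 33% |
| 20% | 0 | 0.800 | 9.6 | 7% |
| 20% | 1 | 0.771 | 9.2 | 12% |
| 20% | 2 | 0.743 | 8.9 | 17% |

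**5. Break-even.** Setting 12 × S = 8 gives d = 1 − (2/3)^(6/(6 + w)). This is 29% for a 1-month wait and 26% for 2 months. Below those losses, 12 still gives an expected 8 or more.

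**6. Number needed at the full one-third.** 8 / S = 12.84 (1 month) or 13.74 (2 months), so 13 or 14 in each of arms 3 and 4. The total would be 44 to 46 instead of 42. Arm 2 stays at 12.

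**7. Link to the top-up.** Fewer than 8 of 12 means at least 5 lost, or 42%, which exceeds 33%. Exactly 8 of 12 means 4 lost, the one-third the plan allows for. So the last column is the chance that the top-up is needed in one arm.

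**The case against.** A reader might infer that 12 per arm is a wrong sample size, or that 8 evaluable cannot be reached. The documents support neither. The figure of 12 follows exactly from the stated inputs and suits arm 2, which has no wait. The top-up also exists to bring each treatment arm to at least 8. Someone who leaves before DT0 is not evaluable for the primary endpoint, so the rule can be read to cover them. Its price, loss of randomisation for the added people, is disclosed.

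The size is also uncertain. One-third is a ceiling, not a forecast. The wait is inferred, and no loss rate is given for it. Even with no wait, treating the ceiling as the true rate gives a 37% chance of falling short, so much of the 50% to 61% comes from that choice. The trial is a descriptive pilot with no power target, and the expected shortfall is 0.5 to 1 person in each of two arms.

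A reader might also infer that knowing the arm will drive people out. Nothing in the protocol shows this. Arms 3 and 4 begin with the same 3-week albendazole course, and participants know their arm from then until the second intervention whatever is done about the wait.

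The residence criterion is a small matter. Its 6-month follow-up period can be read as running from arm start, and only an early recruit assigned to arm 3 or 4 would be needed for 9 to 10 months.

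These points limit the size. They do not supply an allowance for the interval, and the top-up does not cure the problem: it secures the number by adding people who were not randomised.

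**Conclusion.** The point holds for arms 3 and 4 only. Section 5.2 makes no provision for loss between randomisation and the start of these arms, although the design in sections 4.4 and 6.2 creates that interval and discloses the allocation during it. At the full one-third loss there is no reserve.

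Assuming the same monthly loss through a wait of 1 to 2 months, expected evaluable falls by about 0.5 to 1 person per arm, and the chance of needing the top-up rises by about 13 to 24 percentage points (from 37% to 50% or 61%). At 25% loss over 6 months the expected number stays above 8, and the chance rises from 16% to 24% or 33%. With no loss during the wait, nothing changes.

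The consequence is a greater reliance on non-randomised additions in arms 3 and 4, and room for arm-dependent departure before treatment. The latter is a possibility that the design leaves open, not an effect that the documents show. The change is worth making because it costs little.

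**What to change.** 1. **Section 6.2, Randomisation and start of study arms.** At the first randomisation, assign only arm 1 (6), arm 2 (12) or the second wave (24). Open the arm 3/arm 4 envelopes at DT0 of the second wave. Losses during the wait then cannot depend on which of the two arms a person was given.

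2. **Section 5.2.** State the planned interval before arms 3 and 4 start, and that the one-third allowance does not cover it for these arms. Later opening does not itself prevent loss. If the number is to be protected, either replace people who leave before DT0 or enlarge these arms (13 to 14 each under the assumption used above).

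3. **If leavers before DT0 are replaced.** Report that the replacements were randomised only between arms 3 and 4 and could never have entered arm 1 or 2. Exclude them in a sensitivity analysis of comparisons with those arms.

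**Cost.** A two-stage allocation list, and second-wave participants learn their arm later, on their first treatment day. Knowledge of the arm after DT0, including before the second intervention, remains as in any open-label design. Optionally, the residence criterion in section 5.3 could name the span from consent to the end of follow-up. That is a minor wording change.

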## Inclusion criteria

- Adult, participants of either sex
- *L. loa* microfilaria < 50,000 mf/mL
- Intention to remain residing in study area and comply with study procedures throughout 6 month follow-up period
- Signed written informed consent

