# Document history

| **Version (date)** | **Changes** | **Author** |
| --- | --- | --- |
| V1.0 (06-09-2017) | Original version | [name]  [name] |
| V1.1 (08-09-2017) | Update of the trial design and other modifications of the protocol, English + French summary added | [name]  [name] |
| V1.2 (11-10-2017) | Modifications based on CEI review: addition of voluntary treatment option for arm 1 at end of study; addition of recent albendazole intake as exclusion criterion; clarification of (frequency of) follow-up visits in arms 3+4; clarification/addition of blood sampling time points (during initial ‘treatment’ phase in arm 1, at DRT+1 in arm 4 and at month 6 in all study arms); clarification of blood sample volumes; clarification of symptomatic treatment; addition of PCR as mf detection/quantification method; addition of paragraph on subject risk/benefit; limitation of sample storage duration to 5 years; clarification of study monitoring. |  |
| V2(22-01-2018) | Modification of threshold of parasitemia as inclusion criteria: For reasons of patient safety, we have set an upper limit of 50.000mf/l, and the benefit of treatment is also expected for patients with parasitemia less than 10,000 mf / μl. Moreover, for logistical reasons (too far/isolated), refusal to participate we may reduce the threshold of parasitemia below 10.000 mf/µl  Addition of stool and urine samples collection before treatment: We wish to have the intestinal parasitic status of the participants since we will treat with albendazole which also has an effect on many helminths; which could affect the tolerability and influence nonspecific symptoms such as pruritus. Moreover for the immunological evaluation the search of these parasitic infections is necessary to get a complete picture of helminth co-infections. |  |

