### Albendazole (ALB)

Albendazole – a benzimidazole anthelminthic drug - has a broader spectrum of activity and increased oral bioavailability as compared to mebendazole. In a double-blind, placebo-controlled trial ([17](#_ENREF_17)), albendazole at a dose of 400 mg per day for 21 days led to a gradual reduction of microfilarial levels in patients with loiasis to 20% of pre-treatment levels at 6 months. The slow decline in microfilaraemia is consistent with a primary effect on the adult parasites, as has been proposed in other filarial infections. Despite extremely high microfilarial levels in some patients (>50,000 mf/mL of blood), there were no clinical adverse effects and no observed hepatotoxicity, renal toxicity or hematologic abnormalities attributable to the drug. The utility of albendazole in safely reducing the numbers of circulating microfilariae (and presumably the side effects of therapy) prior to definitive treatment with DEC or ivermectin has not yet been examined. Shorter courses of albendazole (1 or 3 days) have been shown to significantly lower microfilarial counts in some studies, although the effect is variable and transient ([18](#_ENREF_18), [19](#_ENREF_19)). Albendazole has also been successfully used in the treatment of 3 patients with symptomatic loiasis refractory to multiple courses of DEC ([20](#_ENREF_20)), and should be considered in the treatment of patients refractory to or intolerant of DEC.

In summary, albendazole appears as a safe option for the treatment of loiasis irrespective of microfilaraemia level. However, appropriate regimens and the sustainability of albendazole’s effect remain to be described appropriately.

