## Endpoints

### Primary endpoints

1. Primary efficacy endpoint will be the proportion of subjects with *L. loa* microfilarial levels <100 mf/mL at 6 months after the commencement of treatment
2. Co-primary efficacy endpoint will be the proportion of subjects without microscopically detectable microfilariae (assessed on three consecutive days) at any time point during follow up.

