# Study population

## Context

All study participants for this treatment trial will be recruited amongst study subjects enrolled in the ongoing Burden of Disease in *Loa loa* (BuDiLoLo) study. The aims and design of this study are described the BuDiLoLo study protocol. Briefly, the primary objective of the BuDiLoLo study is to assess the burden of disease, including DALYs lost and economic impact, caused by *Loa loa* on the local population in central Gabon. The study is cross-sectional in design and based in & around the town of Fugamou in the Tsamba-Magotsi department, Ngounié province and in the neighbouring Moyen-Ogooué province, Gabon. Ngounié is considered highly endemic for *L. loa*, with an estimated prevalence of +-18% ([3](#_ENREF_3), [24](#_ENREF_24)); in contrast, Moyen-Ogooué is considered low-endemic for loiasis. 1000-2500 subjects of all ages (≥2 years) from randomly selected households in a random sample of villages will be included with the target of obtaining ≥700 *Loa*-infected individuals. Subjects will be interviewed using the WHO-validated RAPLOA questionnaire and a single blood draw will be performed for amongst others the detection/quantification of *L. loa* and *Mansonella* spp. microfilaria by thick smear microscopy, leukocyte concentration techniques and PCR.

Adult both sex subjects with *L. loa* infection levels < 50,000 mf/mL will be considered eligible for participation in the treatment study. Once sufficient participants are included for the entire study design (see below), they will be randomized to one of four study arms, which will commence semi-sequentially as described above.

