## Recruitment & informed consent

Adult male subjects in the BuDiLoLo study found to be harbouring *L. loa* microfilariaemia < 50,000 mf/mL will be approached by study team with regards to possible participation in the trial. The aims, design, in- & exclusion criteria and procedures of the trial will be provided to them in written form as well as explained to them in understandable terms and they will be given adequate time (≥2 days) to consider.

If following this period they are still interested in participating, potential participants will be invited for a screening visit where they will first be asked to sign a written informed consent form. In the case of illiterate participants, an impartial witness will be asked to co-sign the consent form.

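### Entry has no lower limit on microfilaraemia, so a person already under the primary endpoint threshold of 100 mf/mL can enrol and count as a success without any drug effect

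*Protocol*

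**What the plan says.** **Entry.** Section 5.3 of the protocol gives the load criterion as "microfilaria < 50,000 mf/mL". The exclusion list in 5.4 sets no minimum. The other statements of eligibility also give only the upper bound: the summary (1.1), the trial overview (4.1), the context section (5.1: "infection levels < 50,000 mf/mL will be considered eligible for participation in the treatment study") and the recruitment section (5.5: "microfilariaemia < 50,000 mf/mL will be approached by study team"). The screening visit (6.2) confirms the count but sets no pass mark.

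**Primary endpoint.** Section 4.3.1 counts subjects with "microfilarial levels <100 mf/mL at 6 months after the commencement of treatment". This is an absolute level with no reference to the starting count.

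**Aim.** The primary objective (4.2.1) is efficacy in reducing loads. The study-size section (5.2) speaks of a sustained reduction.

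**Measurement.** The feeder study finds carriers by thick smear and also by "leukocyte concentration techniques and PCR". In this trial (6.4.1) the smear uses 10 µL, and smear-negative samples in principle go to a saponin read of 1 mL. Loads of 1–99 mf/mL can therefore be measured.

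**Design.** Allocation is 6 controls and 12 in each of three treatment arms, and no stratification by load is stated (6.2, Randomisation).

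**The concern.** The objective is about reduction, but the primary endpoint can be met with no reduction at all. A person who enters at 90 mf/mL and is still at 90 mf/mL six months later is a success, even in the control arm. A person who falls from 10,000 to 2,000 mf/mL is a failure despite an 80% drop.

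The trial exists to identify regimens worth taking into larger trials, and the proportion per arm is its headline result. With 12 people per treatment arm and 6 controls, a few low-load entrants falling unevenly could create or hide a difference between regimens. An analysis plan can describe this afterwards, but it cannot change who was enrolled.

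**Working it through.** **1. The plan's own figure.** 8 evaluable per treatment arm with one third lost gives 8 / (1 − 1/3) = 12. The total is 6 + 3 × 12 = 42. Both match section 5.2. The protocol states no power calculation; the study is descriptive.

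**2. Who is already below the threshold.** One microfilaria seen in 10 µL corresponds to 1 × 1,000/10 = 100 mf/mL, which is not below 100. A count of 1–99 mf/mL is thus typically a sample that is negative on smear and positive on the 1 mL saponin read. Nothing in 5.3 or 5.4 keeps such a person out.

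**3. Highest baseline that ends below 100 mf/mL.** The formula is 100 / (fraction of baseline remaining). The first line uses the result cited in section 3.2.3: "to a gradual reduction of microfilarial levels in patients with loiasis to 20% of pre-treatment levels at 6 months", at 400 mg per day. The others are assumed stronger effects, because the trial gives 400 mg bid and adds second-stage treatment in arms 3 and 4.

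| Fall from baseline | Limiting baseline (mf/mL) |
| --- | --- |
| 80% (cited) | 100/0.20 = 500 |
| 90% (assumed) | 100/0.10 = 1,000 |
| 95% (assumed) | 100/0.05 = 2,000 |
| 99% (assumed) | 100/0.01 = 10,000 |

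From the upper limit of 50,000 mf/mL the fall needed is 1 − 100/50,000 = 99.8%.

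For arm 4, take the cited ivermectin reduction of 70–90% (3.2.2) and assume it multiplies the albendazole effect. The limit is then 100/(0.20 × 0.30) = 1,667 to 100/(0.20 × 0.10) = 5,000 mf/mL.

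**4. One drug effect, different baselines.** This step rests on assumptions: log-normal baselines (log-SD 1.5–2.0) cut at 50,000 mf/mL, an 80% typical fall, and person-to-person variation of log-SD 0.7. Simulated success is 67–71% for a median baseline of 200 mf/mL, 34–38% for 1,000 and 4–10% for 10,000. The shares with a baseline under 500 mf/mL are nearly the same: 68–73%, 32–37% and 3–9%.

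**5. Chance imbalance under unstratified allocation.** Let L of the 42 be low-load. The numbers a and b falling in two given arms of 12 have probability C(12,a) C(12,b) C(18,L−a−b) / C(42,L). Summing over |a − b| ≥ 3 gives the middle column. The chance that the control arm receives none is C(36,L)/C(42,L).

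| L (assumed) | Two given arms differ by 3 or more | No low-load control |
| --- | --- | --- |
| 3 | 0.04 | 0.62 |
| 6 | 0.15 | 0.37 |
| 10 | 0.24 | 0.17 |
| 14 | 0.28 | 0.07 |

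**6. What three people are worth.** The shift is 3/12 × (success rate in low-load − success rate in others). The maximum is 3/12 × (1 − 0) = 25 percentage points. With assumed rates of 90% and 30% it is 3/12 × 0.60 = 15 points.

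**The case against.** **Low loads were admitted on purpose.** The version 2 entry in the document history gives logistics and refusals as reasons, but also says that "benefit of treatment is also expected for patients with parasitemia less than 10,000". This stands as a reason for lowering the old threshold. It does not explain why there is no minimum at all. An absolute target is also defensible for a programme concerned with transmission and safe mass treatment (4.2).

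**The protocol has partial safeguards.** Randomisation protects the contrast between arms on average. The control arm is recruited under the same criteria. DT0 counts are taken, and median reduction is a secondary endpoint (4.3.2). All of this stands, but 6 controls and 12 per arm make the first two weak, and the secondary endpoint does not repair the primary one.

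**Stronger readings that the protocol does not support.**

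- A reader might infer that the primary endpoint measures baseline load instead of drug effect. That is true only for entrants already below 100 mf/mL; for others it reflects both.
- A reader might take 25 points as the expected distortion. It is the ceiling for an imbalance of three, reached only if every low-load person succeeds and everyone else fails.
- A reader might conclude that only people under 500 mf/mL can succeed. That turns a group figure at another dose into a constant for individuals, and it leaves out the second-stage treatments.
- A reader might assume that PCR-only carriers will enrol. Section 5.5 approaches people found to carry microfilariae, and screening confirms the count, so a PCR signal alone does not make someone eligible.
- A reader might say that the trial will choose the wrong regimen. It is descriptive, looks for promising regimens in the plural, and reports several other endpoints, including the co-primary ("without microscopically detectable microfilariae (assessed on three consecutive days) at any time point during follow up").

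**Conclusion.** The point holds as a should-fix. Eligibility has no floor, and the primary endpoint is an absolute level, so people with 1–99 mf/mL can enter and be counted as successes without any treatment effect. That follows from the text and needs no assumption beyond their load staying below 100 mf/mL. For higher baselines, success depends on both starting load and drug effect, and the balance between them shifts with how strong the trial's regimens prove to be.

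The size of the effect on the results is uncertain because the protocol gives no baseline distribution. Over 3 to 14 low-load people among 42, the chance that two given arms differ by three or more of them runs from 0.04 to 0.28, for a shift of no more than 25 points. If almost nobody below 100 mf/mL enrols, the first problem disappears in practice, and only the mixing of baseline and effect remains.

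**What to change.** 1. **Entry.** Add to section 5.3 a minimum microfilarial count at the confirmatory screening visit, clearly above the 100 mf/mL endpoint threshold, with the value set by the sponsor. Align sections 1.1, 1.2, 4.1, 5.1 and 5.5 with it.
2. **Analysis set.** Keep all randomised participants in the primary analysis. Add a sensitivity analysis without anyone below 100 mf/mL at DT0. Removing such people from the primary analysis would mean exclusions after open-label randomisation and would erode the 8 evaluable per arm.
3. **Reporting.** Show the primary proportion beside the change from DT0, adjusted for the log DT0 count. A floor alone does not remove the dependence on baseline, so this step is needed as well. The counts are already collected.

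The cost is one line in the inclusion criteria, matching edits elsewhere and a short analysis statement, with no extra visits or samples. The downside is that some very low-load carriers will not be recruited, and the higher the floor, the more are lost.
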